#### Participant Exclusion Criteria:

1. Unsuitable cognitive capacity as judged by the study physician;
2. Diagnosis of neurological injury other than SCI, such as stroke, traumatic brain injury; or other neurological condition that the study physician considers to be exclusionary;
3. Multiple spinal cord lesions;
4. History of frequent autonomic dysreflexia;
5. History of seizures;
6. Use of medications that significantly lower seizure threshold, such as anti-psychotics, tricyclic antidepressants, amphetamines, and bupropion;
7. History of implanted brain/spine/nerve stimulators, aneurysm clips, or cardiac pacemaker/defibrillator;
8. Deep vein thromboses in lower extremities of less than 6 months duration;
9. Pregnancy;
10. (Interventional phase only): Lack of detectable tibialis anterior MEP at baseline even with active facilitation;
11. (Interventional phase only): Inability to maintain supported upright posture without symptoms of orthostatic hypotension (light-headedness, pre-syncope);
12. (Interventional phase only): Active pressure ulcers greater than stage 1 severity on the foot, ankle, knee and/or pelvic girdle;
13. (Interventional phase only): Bone mineral density of the hip (proximal femur) T-score <3.5 SD from age- and gender-matched normative data;
14. (Interventional phase only): Any spasticity, contractures, or heterotopic ossification that result in inadequate range of motion of the shoulder, elbow, wrist, fingers, hip, knee, or ankle joints in the judgment of the study physician;
15. (Interventional phase only): Inability to cooperate with instructions or unwilling to commit to training sessions for three-four days per week over roughly 9 months;
16. (Interventional phase only): A diagnosis of coronary artery disease that precludes moderate to intense exercise.

**Recruitment:**

Recruitment will be accomplished by pre-existing relationships, physician referrals, and IRB-approved advertisements. Veterans with SCI who have an ongoing relationship with the Center of Excellence for the Medical Consequences of SCI, such as those who attend the pulmonary, endocrine, cardiovascular, and gastroenterology clinics, will be informed about the study. Physicians at the James J. Peters VA Medical Center will be informed of the goals and aims and the inclusion/exclusion criteria for this study. We will not contact any patients unless referring physicians provide us with assurance that the patient would be interested in receiving further information about this study.

**Eligibility Screening:**

Persons with SCI interested in participating will be assigned a number beginning at 001. No PHI will be collected at that time. To determine eligibility, interested participants will be asked the “yes” or “no” questions listed below. Persons who answer “no” to any of the following questions will not be eligible for the study:

- Do you have a cervical or thoracic spinal cord injury (SCI)?
- Did your SCI occur greater than 12 months ago?
- Are you between the ages of 21 to 65 years?
- Are you legally able to sign for your own consent?

If the potential participant answers “yes” to all questions, then the informed consent process will continue by inviting the participant for an in-person interview.

**Enrollment:**

At the in-person interview, the study will be explained by one of the study team members. All study team members will be trained to obtain consent. The study will be explained in its entirety. The study team member will explain that the training regimens are being studied for investigational purposes. Along with explaining each of the testing and evaluation procedures, the study team member will explain every possible risk that the participant may encounter. No benefits will be guaranteed.

Included in this explanation will be the necessity for the investigative team to determine study eligibility by “screening” – screening will include a review of the participant’s medical record, a DXA scan, and a physical examination by the study physician. The time commitment that is needed to be a part of this study will also be explained – multiple visits per week for a period of approximately four months. The potential participant will be told that there is a possibility that he or she will not be eligible if any of the exclusion criteria are found to be true (i.e. a screening failure). It will also be explained to the participant that if he or she misses more than 25% of the study visits, then the investigators have the option to remove that person from the study.

Potential participants will be encouraged to ask questions throughout the process. Potential participants will be informed of their right to withdraw at any time and that choosing to not participate will not infringe on any of their regular VA benefits or medical care. Once he/she has no further questions and the study team is confident that the potential participant fully understands the protocol and its risks, then the participant will be asked whether he or she is willing to sign the ICF.

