#### **Interventional Phase: Targeted exercise training for motor-incomplete thoracic SCI**

- A. Interventions:** Participants with motor-incomplete SCI (AIS grade C or D or volitional strength of at least 1/5 in two or more key lower extremity muscles, AND volitional strength of at least 3/5 in shoulder and elbow muscles) or some participants with electromyographic evidence for residual motor circuits will undergo two different exercise training regimens in random order: conventional locomotor treadmill training and multimodal training combining balance training with skilled hand exercises. A harness and two clinicians will be used for support and safety.
  - 1. **LOCOMOTOR:** harness-supported treadmill training.
  - 2. **MULTIMODAL:** staged balance training (to stimulate brainstem postural circuits) plus skilled hand exercises (to simultaneously stimulate corticospinal circuits);
- B. Schedule:** Training sessions of 30 minutes will occur 3-4 times per week for a total of 48 sessions per intervention. The functional and electrophysiological parameters described in Phase 1 will be assessed at the beginning and end of each training period; and 6 weeks after completion of all training.
- C. Primary Outcomes:** Change in tibialis anterior motor evoked potential amplitude; change in lower extremity motor score.
- D. Secondary Outcomes:** Change in AIS sensory score; change in Berg Balance Scale score; change in number of steps taken during Ten Second Step Test; change in gait speed and disability; change in leg spasticity (modified Ashworth Scale, SCATS, and SCI-SET); change in grasp-and-release test or pinch dynamometry (in cervical-level participants); change in pain (McGill Pain Questionnaire); change in quality of life (WHOQOL-BREF and SCIQoL) change in upper and lower extremity lean tissue mass; change in soleus H-reflex facilitation; change in seated and standing posturography; and change in motor control measured by surface electromyography.

We hypothesize that in motor incomplete SCI participants, combinations of exercises simultaneously stimulating corticospinal and brainstem tracts *above* spinal lesions should lead to greater neural recovery *below* lesions than traditional treadmill training.

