**Baseline testing (to be conducted over two visits):**

Once a participant has provided signed informed consent, a detailed review of the participant’s history and medical record will be conducted. A physical exam will be performed, including the Modified Ashworth Scale, the Spinal Cord Assessment Tool for Spasticity (SCATS) (Benz et al. 2005), and the American Spinal Injury Association (ASIA) Impairment Scale (AIS). Further clinical assessments will include the Berg Balance Scale; the Walking Index for Spinal Cord Injury II; the 10-meter walk test; the 10-second seated step test; a modified grasp-and-release test (Wuolle et al., 1994); pinch dynamometry; the Spinal Cord Injury Spasticity Evaluation Tool (SCI-SET) (Adams et al. 2007); the WHOQOL-BREF questionnaire (World Health Organization 1998); SCI-QoL questionnaire (Tulsky et al. 2011); and the

McGill Pain Questionnaire (short form). Depending on the severity of paraparesis, not all Participants will be able to perform the step or walk tests. As such, no baseline walking data will be collected for these outcomes in these participants. To ensure tolerance of upright position, heart rate and blood pressure will be measured for 10 minutes while the Participant is in an upright position supported using an overhead harness or standing frame. A full-body DXA scan will be performed. To be eligible for Phase 2 of the study, results from the DXA of the proximal femur must not have a T-score lower than 3.5SD below age/gender-matched controls. Seated and standing computerized posturography, motor evoked potentials, multiple tests of soleus H-reflex facilitation, and surface electromyography will also be assessed. At this point, the study evaluation is complete for participants with AIS A/B impairment. Only participants with AIS C/D injury or volitional strength of at least 1/5 in two or more key lower extremity muscles or some participants with electromyographic evidence for residual motor circuits will be eligible for the interventional component of our study. If any exclusion criteria are met, or if the participant decides at any time not to continue, he or she will not be further studied.

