### **Training period (48 sessions per intervention separated by a 6-week washout):**

Participants will undergo training with 30-minute sessions during 3-4 visits per week. Participants will have the option of performing up to two training sessions per visit to our center, with a break of at least 45 minutes between sessions. The two training paradigms will consist of 1) LOCOMOTOR training and 2) MULTIMODAL training. Training paradigms are described in detail in the next section.

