### **6-Week Follow-up evaluation:**

All the measures evaluated at the baseline visits will be repeated at six weeks after completion of the second intervention.

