### **Research Design:**

This protocol will investigate the efficacy of combining fine-motor exercises with balance exercises in the rehabilitation of chronic thoracic spinal cord injury patients. There are two phases: an observational phase for participants with either motor complete or incomplete SCI; and an interventional phase for participants with motor incomplete SCI. The observational phase will characterize the residual function of specific neural circuits. The interventional phase will employ a single-group, single-blinded, pre-post-intervention crossover research design. We plan to enroll 51 participants for the observational phase. 24 participants with motor incomplete SCI will continue with the interventional phase, lasting approximately 9 months. The protocol will take 3 years to complete. We hypothesize that participants will demonstrate improved neural connectivity when undergoing multimodal training compared to locomotor training.

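### The enrollment section has staff explain a commitment of about four months, but the crossover as scheduled takes 36 to 44 weeks and the protocol elsewhere says about 9 months

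*Protocol*

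**What the plan says.** The Enrollment section of the protocol describes what the study team member will explain before a candidate signs. Its only statement of duration is "multiple visits per week for a period of approximately four months".

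The rest of the protocol describes a longer commitment for those who train:

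- Specific Aims, Interventional Phase, item B (Schedule): "Training sessions of 30 minutes will occur 3-4 times per week for a total of 48 sessions per intervention".
- Training period heading: "48 sessions per intervention separated by a 6-week washout". The text below it adds an option: "Participants will have the option of performing up to two training sessions per visit to our center".
- Training Schedule (under Training Paradigms): each set of 48 sessions is given at least 12 and at most 16 weeks, with a six-week washout between interventions.
- 6-Week Follow-up evaluation: "All the measures evaluated at the baseline visits will be repeated at six weeks after completion of the second intervention".
- Participant Exclusion Criteria, item 15 (interventional phase only), excludes anyone "unwilling to commit to training sessions for three-four days per week over roughly 9 months". The exclusion list in section 3a repeats this.
- Research Design: the interventional phase lasts approximately 9 months.

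For those who do not train, Baseline testing (planned over two visits) says: "At this point, the study evaluation is complete for participants with AIS A/B impairment". Research Design gives the numbers: "We plan to enroll 51 participants for the observational phase", of whom 24 continue to the interventional phase.

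**The concern.** The four-month figure and the 9-month figure describe the same commitment and differ by more than a factor of two. Four months is close to one training block, yet every participant in the interventional phase is scheduled for both.

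This figure is what staff are told to convey at the consent interview. For a person with chronic spinal cord injury who must travel to the center 3 to 4 days a week, duration matters to the decision to join. The same team must also apply exclusion criterion 15, which turns on willingness to commit for roughly 9 months. Agreement to four months does not establish that the criterion is satisfied.

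**Working it through.** **Inputs**

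| Item | Value | Where in the protocol |
|---|---|---|
| Duration explained at consent | about 4 months | Enrollment |
| Sessions per intervention | 48, at 3 to 4 per week | Interventional Phase, B. Schedule; Training Schedule |
| Permitted block length | 12 to 16 weeks | Training Schedule |
| Blocks per participant | 2 | Randomization |
| Washout | 6 weeks | Training period; Training Schedule |
| Final evaluation | 6 weeks after block 2 | 6-Week Follow-up evaluation |
| Duration stated elsewhere | about 9 months | Exclusion criteria (both lists); Research Design |

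**Conversion.** One month = 365.25/12/7 = 4.348 weeks. Four months = 17.4 weeks; nine months = 39.1 weeks.

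**Block length.** 48/4 = 12 weeks and 48/3 = 16 weeks, which matches the stated limits.

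**Which part of the schedule gives four months?**

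| Span | Shortest | Longest | Months |
|---|---|---|---|
| One block | 12 weeks | 16 weeks | 2.8 to 3.7 |
| Two blocks, training weeks only | 2×12 = 24 | 2×16 = 32 | 5.5 to 7.4 |
| Two blocks plus washout | 24+6 = 30 | 32+6 = 38 | 6.9 to 8.7 |
| Two blocks, washout and follow-up | 30+6 = 36 | 38+6 = 44 | 8.3 to 10.1 |

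Only a single block comes near four months. Nine months falls inside the range for the full schedule.

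**Size of the gap**

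- Against training weeks, when visits are frequent: 17.4/32 = 54% to 17.4/24 = 72%.
- Against the whole calendar span: 17.4/44 = 40% to 17.4/36 = 48%.

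**Loosest reading.** Suppose every visit holds two sessions and the 12-week minimum is not a floor.

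- Block length: 48/8 = 6 to 48/6 = 8 weeks.
- Training weeks: 2×6 = 12 to 2×8 = 16 (2.8 to 3.7 months).
- Last session, with the washout in between: week 12+6 = 18 to 16+6 = 22 (4.1 to 5.1 months).
- Follow-up evaluation: week 18+6 = 24 to 22+6 = 28 (5.5 to 6.4 months). Four months is then 17.4/28 = 62% to 17.4/24 = 72% of the total.

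**Observational phase.** Participants who stop there have baseline testing over two visits, so several visits a week for four months cannot describe them either. The plan expects 51 − 24 = 27 such participants (27/51 = 53%).

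**The case against.** Four points can be made for the text as it stands.

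- **Like for like.** The phrase concerns a period of several visits per week, while the 36 to 44 weeks include a washout and a follow-up interval without training. This is right: the fairer comparison is with the 24 to 32 training weeks. Four months still falls short of the shorter of these by 24 − 17.4 = 6.6 weeks.
- **Doubled sessions.** If a participant did two sessions at every visit and the 12 weeks were an allowance rather than a floor, the training weeks would come to 12 to 16, which fits the phrase. But doubling is optional, so it cannot be the commitment explained to everyone, and a stated minimum of 12 weeks is most naturally a floor. Those training weeks would also be split by the washout, and the total of 24 to 28 weeks would disagree with the 9 months stated elsewhere. The protocol would remain inconsistent.
- **Other safeguards.** The Enrollment section also requires a full explanation of the study, invites questions, and asks the team to be confident that the candidate understands. Criterion 15 is a second route by which a candidate may hear nine months. The consent form is not available here and may be correct. These points stand and limit the likely harm. They do not correct a specific wrong figure placed beside the general instruction.
- **Observational-only participants.** The 27 add little to the four-versus-nine conflict. That is fair; they show only that the phrase does not describe that group.

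**Conclusion.** The four-month figure is wrong as written. Taking the 12-week minimum as a floor and both blocks as completed, the interventional commitment is 36 to 44 weeks (8.3 to 10.1 months), including 24 to 32 weeks of frequent visits. The figure covers roughly one of the two blocks and contradicts the 9 months stated in three other places, one of them the eligibility criterion that depends on it.

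The severity is minor to moderate. The error lies in an operative consent instruction and should be corrected, but the governing duration is stated consistently elsewhere. How many candidates would actually be misinformed cannot be judged without the consent form. No effect on power, analysis or retention is claimed.

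**What to change.** In the Enrollment section, replace the four-month phrase with text along these lines:

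> Approximately 9 months for the interventional phase: two training blocks of 12 to 16 weeks with visits 3 to 4 days per week, a 6-week washout between them, testing at the start and end of each block, and a final evaluation 6 weeks after the second block. Participants in the observational phase only attend baseline testing over two visits.

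If doubled sessions are meant to shorten a block below 12 weeks, the Training Schedule should say so and the durations should be restated. Otherwise nothing else in the protocol needs to change. Check that the consent form gives the same duration.

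The cost is one phrase and one document check. Some candidates may decline once they hear the full duration, but they would be doing so on correct information.

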**Baseline testing (to be conducted over two visits):**

Once a participant has provided signed informed consent, a detailed review of the participant’s history and medical record will be conducted. A physical exam will be performed, including the Modified Ashworth Scale, the Spinal Cord Assessment Tool for Spasticity (SCATS) (Benz et al. 2005), and the American Spinal Injury Association (ASIA) Impairment Scale (AIS). Further clinical assessments will include the Berg Balance Scale; the Walking Index for Spinal Cord Injury II; the 10-meter walk test; the 10-second seated step test; a modified grasp-and-release test (Wuolle et al., 1994); pinch dynamometry; the Spinal Cord Injury Spasticity Evaluation Tool (SCI-SET) (Adams et al. 2007); the WHOQOL-BREF questionnaire (World Health Organization 1998); SCI-QoL questionnaire (Tulsky et al. 2011); and the

McGill Pain Questionnaire (short form). Depending on the severity of paraparesis, not all Participants will be able to perform the step or walk tests. As such, no baseline walking data will be collected for these outcomes in these participants. To ensure tolerance of upright position, heart rate and blood pressure will be measured for 10 minutes while the Participant is in an upright position supported using an overhead harness or standing frame. A full-body DXA scan will be performed. To be eligible for Phase 2 of the study, results from the DXA of the proximal femur must not have a T-score lower than 3.5SD below age/gender-matched controls. Seated and standing computerized posturography, motor evoked potentials, multiple tests of soleus H-reflex facilitation, and surface electromyography will also be assessed. At this point, the study evaluation is complete for participants with AIS A/B impairment. Only participants with AIS C/D injury or volitional strength of at least 1/5 in two or more key lower extremity muscles or some participants with electromyographic evidence for residual motor circuits will be eligible for the interventional component of our study. If any exclusion criteria are met, or if the participant decides at any time not to continue, he or she will not be further studied.

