##### Phase 2: Targeted exercise interventions

1. Age between 21 and 65 years;
2. Chronic thoracic SCI (levels C2-T12; more than 12 months since injury);
3. AIS grades C or D or volitional strength of at least 1/5 in two or more key lower extremity muscles; or some participants with electromyographic evidence for residual motor circuits;
4. Strength of at least 3/5 in shoulder and elbow muscles;
5. Able to tolerate standing with support;
6. Morphologically capable of fitting a weight-support harness and robotic treadmill system: measurements of the greater trochanter to lateral epicondyle between 35-47 cm for placement in the thigh cuffs; pelvic width >50 cm; thigh circumference above the knee <57 cm; and body mass <135 kg.

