### **Secondary outcomes:**

1. Change from baseline in AIS sensory scores.
2. Change from baseline in Berg Balance Scale score.
3. Change in leg spasticity on modified Ashworth Scale, Spinal Cord Assessment Tool for Spasticity, and Spinal Cord Injury Spasticity Evaluation Tool.
4. Change in gait speed on 10-meter Walk Test.
5. Change from baseline in Walking Index for Spinal Cord Injury II (WISCI II) scale.

6. Change from baseline in total number of steps taken by both feet during seated 10-second step test.
7. Change from baseline in total number of successful grasp-and-release trials taken by each hand (for cervical-level participants only).
8. Change from baseline in pinch dynamometry strength (in cervical-level participants only).
9. Change in quality of life as determined by WHOQOL-BREF and SCIQoL questionnaires.
10. Change in subjective pain as determined by McGill Pain Questionnaire (short form).
11. Change in percentage of upper and lower extremity lean tissue mass.
12. Change from baseline in endpoint excursion and directional control parameters achieved during seated Limits of Stability testing.
13. Change from baseline in soleus H-reflex facilitation and inhibition using appropriately timed physical stimuli, subthreshold transcranial magnetic stimulation, peroneal and tibial nerve stimulation.
14. Change from baseline in the Voluntary Response Index (VRI) for key leg muscles as detected by surface electromyography (Lee et al. 2004).

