### **Statistical Analysis:**

For the observational phase, exploratory analyses will be undertaken to determine how well scores on the electrographic outcomes (evoked potentials, H-reflex testing, computerized posturography, surface electromyography) correlate with clinical outcomes such as gait disability, gait speed, and AIS motor and sensory scores. Using post hoc regression analysis, we hope to generate a preliminary model to predict anatomical and functional integrity of specific neural tracts based on performance on this battery of tests. This analysis and any resulting predictive model would need further validation with a prospectively studied population. The interventional phase of the study would not depend on the success of obtaining such a predictive model.

For the interventional phase of the study, participants will be randomly assigned to receive either locomotor training followed by multimodal training, or multimodal training followed by locomotor training. The primary outcomes will be change in tibialis anterior motor-evoked potential amplitude and change in lower extremity motor score (LEMS) compared to baseline. All other outcomes are secondary and exploratory.

The most rigorous method of analyzing data from crossover studies involves the use of independent-sample rather than paired-sample tests (Wellek & Blettner 2012). Therefore, outcome measures will be calculated within each subject as the percent change between baseline and completion of each intervention. The percent change across all subjects for each training modality will be compared using independent-sample t-tests or Mann-Whitney U tests depending on the normality of the data distribution. To test for the possibility that the washout period does not fully eliminate carryover effects, the percent change across all subjects for each training period (pre-washout, post-washout) will also be compared using independent sample tests. Statistical significance for all outcomes will be corrected for multiple comparisons using Bonferroni's method.

**Power Calculation:** Given that our training protocol is novel, we need to make predictions by extrapolating from other types of protocols. This is further hampered by the fact that most SCI

rehabilitation studies involve rather small numbers of participants in often inadequately controlled studies.

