**Clinical Tests**

- Physical Examination – A standard physical and neurological exam will be performed. This will include seated and upright blood pressure testing.
- American Spinal Injury Association (ASIA) Impairment Scale – Manual assessment of muscle strength in the arms and legs, as well as assessment for sensation in the arms, trunk, legs, and perineal area.
- Modified Ashworth Scale – Leg muscle spasticity will be qualitatively assessed during the clinical exam on a scale of 0 to 4.
- Spinal Cord Assessment Tool for Spasticity (SCATS) – Three components of spasticity in the lower extremity – clonus, extensor spasm, and plantar response – will be timed in response to standardized evocative maneuvers (Benz et al. 2005).

- Berg Balance Scale – Balance and postural stability will be qualitatively assessed in seated, lying, and standing positions. Most patients will not be able to perform the standing portions of the scale. See **Table 1** for details of seated balance section.
- 10-meter walk test (10MWT) – Ambulatory participants will be asked to walk 10 meters at their best pace. The time to cover this distance will be timed with a stopwatch. Assistive devices will be used if necessary – participants using an assistive device at baseline will be retested with the same assistive device at follow-up visits after training.
- Walking Index for Spinal Cord Injury II – Participants will be graded on a scale of 0-20 based on the degree of assistive device support required for walking 10 meters (Ditunno Jr. et al. 2007).
- Seated 10-second step test – Participants with the ability to move their legs will be seated with their hips and knees flexed to 90 degrees. Steps will consist of lifting one foot entirely off the ground and placing it back down again. The average number of steps taken during three 10-second trials with each foot will be recorded.
- Grasp-and-release test – Participants with cervical-level injury in seated position will be asked to grasp a standardized bottle, pick it up, move it approximately 25 cm, then place it down and release. The average number of successful grasp-and-releases taken during three 30-second trials with each hand will be recorded.
- Pinch dynamometry – In participants with cervical-level injury, pinch strength will be recorded using a wireless dynamometer (JTech Freedom Tracker). The average of three maximal pinch strengths in each hand will be recorded.

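### Participants who cannot walk or step at entry get no baseline for gait speed or step count, so a gain made in period 1 cannot be counted for the training that produced it

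*Protocol*

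**What the plan says.** The Protocol's Baseline testing section expects that, depending on severity, "not all Participants will be able to perform the step or walk tests", and continues: "As such, no baseline walking data will be collected for these outcomes in these participants". Under Clinical Tests the 10-meter walk has a restricted population ("Ambulatory participants will be asked to walk 10 meters at their best pace"), and the seated step test is for those who can move their legs.

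Entry to the crossover does not require walking or stepping. The Phase 2 inclusion criteria accept "AIS grades C or D or volitional strength of at least 1/5 in two or more key lower extremity muscles", and also some participants on electromyographic evidence alone.

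Gait speed on the 10-meter walk and the seated step count are secondary outcomes. The Post-training evaluation section repeats the baseline measures at the start and end of each training period. The Statistical Analysis section turns each outcome into a within-person percentage change from baseline to the end of each training and compares the trainings on it. For Phase 1, the same section examines how well the electrophysiological measures "correlate with clinical outcomes such as gait disability, gait speed, and AIS motor and sensory scores".

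WISCI II stands apart. It is a secondary outcome ("Change from baseline in Walking Index for Spinal Cord Injury II (WISCI II) scale"), and Clinical Tests says of it: "Participants will be graded on a scale of 0-20 based on the degree of assistive device support required for walking 10 meters". The Observational Phase list in Specific Aims restricts the 10-meter walk and the step test to subgroups but places no restriction on WISCI II.

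**The concern.** Being unable to walk or take a seated step is a result, and on a speed or a count it has a natural value of zero. The Protocol leaves it blank. A change score needs a starting value, so a person who could not walk at entry and can walk after period 1 has no period-1 change. Whether a value is missing then depends partly on how well the training worked. If one training restores walking or stepping more often than the other, it loses more of its best results, and randomizing the order does not repair that.

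Phase 1 has a related problem. Leaving non-walkers out of the correlations with gait speed cuts off the most impaired end of the range, and any preliminary predictive model would not be fitted to them.

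The rule governs data collection. If inability is not recorded at the visit, a later analysis plan may be unable to tell it from a test skipped for another reason.

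**Working it through.** **1. The plan's own figure.** The Protocol gives no number for the gait outcomes. Its one calculation concerns motor evoked potential amplitude: 50% versus 25%, variability 25% (read as an SD), 18 subjects, two-tailed α = 0.05, power above 80%. With 18 values per modality, because each person supplies both, power is 0.85 (normal approximation) or 0.83 (t test). The figure reproduces, and the present point does not touch it.

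**2. One participant followed through the rules.** Assumed speeds: cannot walk at entry; 0.20 m/s at the end of period 1; 0.20 m/s after washout; 0.22 m/s at the end of period 2.

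| Rule | Period 1 | Period 2 |
|---|---|---|
| No entry value, own baseline per period, percent change | not computable | (0.22 − 0.20)/0.20 = +10% |
| No entry value, study-entry baseline, percent change | not computable | not computable |
| Entry scored 0, own baseline per period, percent change | 0.20/0, undefined | +10% |
| Entry scored 0, own baseline per period, absolute change | 0.20 − 0 = +0.20 m/s | 0.22 − 0.20 = +0.02 m/s |

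Only the last row credits the gain to the training that produced it. The third row shows that a floor score alone changes nothing while percent change is kept.

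**3. Effect on the modality comparison, on assumed inputs.** 18 completers, 9 per order. Share of non-walkers f = 25%, 50% or 75%. Chance of gaining walking 30% with multimodal (pM) and 10% or 0% with locomotor (pL). Newly gained speed 0.20 m/s. People already walking at the start of a period gain 0.05 m/s on average (SD 0.05) with either training; entry walkers start at 0.50 m/s. Own baseline per period, nothing lost in washout, 3,000 simulated trials per setting, change in m/s.

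- Extra locomotor values created by the rule: 9 × f × (pM − pL). This gives 9 × 0.25 × 0.20 = 0.45 at the low end and 9 × 0.75 × 0.30 = 2.03 at the high end. Simulated: 0.42 to 2.01.
- Difference when scored from 0, middle case (f = 0.5, pM = 0.3, pL = 0.1). Non-walkers' mean change with multimodal is 0.3 × 0.20 = 0.060 if it comes first and 0.1 × 0.05 + 0.9 × 0.060 = 0.059 if second, average 0.0595. With locomotor it is 0.1 × 0.20 = 0.020 if first and 0.3 × 0.05 + 0.7 × 0.020 = 0.029 if second, average 0.0245. The difference is 0.0350, and 0.5 × 0.0350 = 0.0175 m/s. Simulated: 0.0176.
- Across all settings, scoring from 0 gives 0.009 to 0.040 m/s in favor of the training that restores walking. With the missing rule the mean difference lies between −0.0001 and 0.0009 m/s.

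This simulation used m/s throughout. On the plan's percent scale the same 0.05 m/s gain is 0.05/0.50 = +10% for an entry walker but 0.05/0.20 = +25% for someone who has just begun to walk, so the extra second-period values could also be inflated.

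**4. Numbers left.** If 25%, 50% or 75% of 18 completers have no entry value and none gains walking, 18 × (1 − f) leaves about 14, 9 or 4 values per modality. For a 1-SD effect, t-test power would be 0.72, 0.51 or 0.22.

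**5. Phase 1.** 51 − 24 = 27 participants (53%) are not planned for training. The baseline evaluation ends there for AIS A/B participants. The Protocol does not say how many of the 27, or of the 24, cannot walk.

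**The case against.** The best counter-argument is that gait speed among people who walk is a coherent, openly declared measure. Scoring inability as 0 m/s is a convention that brings many ties, and scoring conventions often belong in an analysis plan. Part of this stands: speed among walkers is worth reporting, and the ties are a real cost. But the Baseline testing sentence decides what is collected, and the change score in the Statistical Analysis section is also fixed in the Protocol.

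The second argument is that percent change from 0 is undefined, so the missing value is not the sole cause. This is right. Both provisions have to change.

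There are also stronger readings that the documents do not support:

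- A reader might infer that all gait information on recovery from non-walking is lost. The Baseline testing section names WISCI II separately from the two tests, the Observational Phase list does not restrict it, and it runs from 0. Non-walkers probably keep a WISCI II baseline, and so the walking-disability measure in Phase 1. The text merely fails to say so.
- A reader might infer that such a person always counts for the opposite training. That needs a baseline for each period and a gain that outlasts the washout.
- A reader might infer that the comparison is reversed. On the m/s scale above it is pulled to about zero.
- A reader might take the 27 participants not planned for training as non-walkers. The Protocol gives no such count. Its remark on the Berg scale, "Most patients will not be able to perform the standing portions of the scale", suggests the group is not small, but it concerns standing items.

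**Conclusion.** The point holds for gait speed on the 10-meter walk and for the seated step count. As written, a participant who moves from unable to able in period 1 supplies no change for that training on either meaning of baseline. The affected comparisons omit these gains in a way that depends on response, and the Phase 1 correlations with gait speed omit non-walkers.

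The logic rests on the text; the size does not. The Protocol states neither the share of non-walkers nor a rate of regaining walking more than 12 months after injury, so the 0.009 to 0.040 m/s range is only an illustration of assumed inputs. The outcomes concerned are secondary and exploratory, and any Phase 1 model is described as needing further validation. The primary outcomes and the sample size are unaffected. This is worth correcting, but it does not threaten the main result.

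**What to change.** **Baseline testing section.** Replace the sentence on uncollected data with a rule of this kind: a participant unable to perform a test is recorded at its lowest value (0 m/s for the 10-meter walk, 0 steps for the seated step test) at every assessment where this applies; WISCI II is graded for everyone, with 0 for those who cannot walk; a value is missing only if the test was not done for another reason. Add a field on the case report form that separates the two situations, and align the wording that restricts the tests under Specific Aims and Clinical Tests.

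**Statistical Analysis section.** For these outcomes, use absolute change instead of percent change, state that the baseline is the value at the start of each training period, and compare the trainings with a rank-based test. The section already names the Mann-Whitney test. In Phase 1, include the zeros and use rank correlation. Report gait speed among walkers as a supplementary analysis.

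**Cost.** Edits to two sections with conforming words elsewhere, and one form field. No new test and no added visit. The drawback is tied zeros, which reduce the resolution of the rank comparison. The change should be made before data collection, because inability not recorded at the visit may not be recoverable.
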